### Study visits and procedures

The visit schedule for all evaluations (baseline, primary outcomes, secondary outcomes, exploring outcomes and safety indicators) is shown in Table 1. Participants will be assessed by the same investigator at each assessment. Baseline measurements, demographic characteristics, and medical history will be collected at the first visit only. All concomitant medications will be recorded during the treatment period (i.e., baseline to 8 weeks), including the name, dosage, and course of these medications. Primary and secondary outcomes and safety indicators will be collected every 4 weeks from baseline until week 16.

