## Methods/design

### Study design

This is a double-blind, randomized, placebo-controlled, pilot trial designed to evaluate the safety and efficacy of JDTLG in treating PSD with qi deficiency and blood stasis syndrome. Eighty participants with PSD will be recruited from Xiyuan Hospital of China Academy of Chinese Medical Sciences. After obtaining written informed consent from participants or their legal guardian, participants will be randomly assigned to either the treatment or placebo group with a ratio of 1:1. Participants will undergo an 8-week treatment period and an 8-week follow up. The protocol design is based on the Consolidated Standards of Reporting Trials (CONSORT) guidelines and Standard Protocol Items: Recommendations for Interventional Trials (SPIRIT) Checklist (see Additional file 1).

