### Withdrawal and discontinuation

Participants are able to voluntarily withdraw at any time during the trial. Participants who fail to complete the study, regardless of time or reason, will be considered as dropouts. The last recorded data for these participants will be included in data analyses. Data obtained from participants who experience unrelated complications, such as substantial change in disease status, exacerbation of depression or commence medication that could potentially interfere with JDTLG, will be treated as invalid. Withdrawal due to adverse events will be distinguished from withdrawal due to insufficient response. All adverse effects will be analyzed at the endpoint of the trial regardless of whether they are deemed related to the trial medication or not. If a participant withdraws due to a serious adverse event, it will be reported in accordance with the reporting requirements. Where appropriate, data collected by these participants will be used in intention-to-treat analyses.

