### Intervention

Participants will be allocated to receive JDTLG or placebo for 8 weeks in addition to their usual conventional treatment (e.g., antiplatelet, lipid-lowering, antihypertensive, or antidiabetic therapy). The JDTLG and placebo granules (3.9 g/sachet) will be taken orally with warm water twice a day for 8 weeks. Product will be provided by China Resources Sanjiu Medical and Pharmaceutical Co., Ltd., Shenzhen, China (Production batch number: 161001 W). Analyses have shown that the quality of JDTLG is consistent with the Chinese Medicine Standards of the State Food and Drug Administration (SFDA). Active granules contain 3.9 g of JDTLG each, which is equivalent to 24 g of crude medicine. Placebo granules are composed of 10% crude JDTLG and 90% starch and are of identical appearance and smell as the active granules. Participants will be instructed to refrain from all other Chinese herbal decoctions or medicines used to treat PSD during the study. Participants can withdraw from the study and choose modern medical treatments, such as SSRI antidepressants, when their depressive symptoms worsen. All of the unused granules will be asked to be returned to the trial team and reasons of not taking the medicine will be recorded on the CRF.

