#### Secondary outcomes

Improvement in neurological function at each appointment throughout the trial. Efficacy will be determined by a reduction of ≥ 50% or the total score of 0–1 in the 15-item National Institute of Health Stroke Scale (NIHSS) score (scores range from 0 to 42, whereby higher scores indicate a more severe neurological deficit) [27]The improvement in independence at each appointment as measured by a modified Rankin Scale (mRS) at each appointment throughout the trial (scores on this scale range from 0 to 6, with higher scores indicating greater disability) [28]The proportion of participants with a Barthel Index (BI) score of ≥ 90 at each appointment throughout the trial. The BI is used to evaluate the activities of daily living, ranging from 0 to 100, whereby higher scores indicate increased independence [29]The improvement of TCM syndrome at each appointment as measured by the reduction (reduction = (before treatment score − after treatment score)/before treatment score × 100%) in the following scale: clinical cure: reduction > 75%, markedly effective: reduction 51–75%, effective: reduction 25– 50%, invalid: reduction < 25% [30]

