### Statistical analysis

All of the data from this study will be analyzed by biostatisticians using SPSS 20.0 (IBM Corp., Armonk, NY, USA). Outcomes are based on the intention-to-treat analysis.

Baseline characteristics will be summarized by means of simple descriptive statistics and be compared between two study groups to assess covariate balance. The two-sample Student’s *t* test will be used for continuous variables and the chi-square test or Wilcoxon test will be used for categorical variables.

The primary analysis will be a comparison of the efficacy on depression between the two groups after 8 weeks of treatment. Pearson’s chi-squared test will be used to analyze the effective cases and logistic regression will be used to adjust for chance imbalances in the main prognostic variables between groups, such as age and gender.

Secondary analyses will include the improved cases in neurological function (NIHSS score reduction of ≥ 50% or the total score of 0–1), independence (mRS 0, 1, and 2), daily living (BI scores ≥ 90), and TCM syndrome. Secondary outcome analyses will be carried out according to standard statistical principles for comparison of parametric or non-parametric distributions as appropriate. Logistical regression analysis will be used to adjust for chance imbalances in the main prognostic variables between groups, such as age, NIHSS scores, BI scores, and TCM syndrome scores.

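### Concomitant medication is recorded only to week 8, although secondary outcomes and safety are assessed to week 16, so treatments started in follow-up could bias those results without a record

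*Protocol article*

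**What the plan says.** Study design sets the two periods: "Participants will undergo an 8-week treatment period and an 8-week follow up".

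Study visits and procedures then gives two different windows in consecutive sentences. For co-treatment: "All concomitant medications will be recorded during the treatment period (i.e., baseline to 8 weeks"), covering name, dosage and course. For outcomes and safety: "Primary and secondary outcomes and safety indicators will be collected every 4 weeks from baseline until week 16".

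Secondary outcomes places NIHSS, mRS, Barthel Index and TCM syndrome at every appointment; the first item reads "Improvement in neurological function at each appointment throughout the trial". The depression endpoint is different. Statistical analysis fixes it at the end of treatment: "The primary analysis will be a comparison of the efficacy on depression between the two groups after 8 weeks of treatment".

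Three further statements bear on other treatment:

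- Intervention: "Participants will be instructed to refrain from all other Chinese herbal decoctions or medicines used to treat PSD during the study".
- Intervention: "Participants can withdraw from the study and choose modern medical treatments, such as SSRI antidepressants, when their depressive symptoms worsen".
- Withdrawal and discontinuation: data from participants who "commence medication that could potentially interfere with JDTLG, will be treated as invalid".

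**The concern.** Study product ends at week 8. A participant who is still depressed then has a plain reason to try something else, and at that moment the protocol stops asking what is being taken. Entry requires no psychotropic drug in the preceding month, so an antidepressant first taken in weeks 8 to 16 would be a new treatment rather than background.

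Two things are at stake. First, if starts differ between arms, or if non-responders are the ones who start and there are more of them in one arm, the week 12 and 16 comparisons mix the randomised treatment with later co-treatment. Second, the Background section itself lists bleeding, stroke, nausea, diarrhoea, fatigue and dizziness as antidepressant effects. An adverse event of that kind in follow-up could not be read correctly without knowing whether such a drug had been started. A favourable safety profile is part of the rationale for the granules, so this matters even in a pilot.

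**Working it through.** No stated figure is in dispute. The check compares time windows, then gauges how large the effect could be under assumptions.

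**Step 1. Windows side by side.** Post-baseline visits every 4 weeks to week 16 fall at weeks 4, 8, 12 and 16.

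| Item | Weeks covered | Source section |
|---|---|---|
| Study product | 0–8 | Study design; Intervention |
| Concomitant medication record | 0–8 | Study visits and procedures |
| Primary depression comparison | 8 | Primary outcome; Statistical analysis |
| HAMD-17 collection | 0–16 | Study visits and procedures |
| NIHSS, mRS, BI, TCM syndrome | every appointment, to 16 | Secondary outcomes; Study visits and procedures |
| Safety indicators | 0–16 | Study visits and procedures |

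Visits with outcomes but no medication record: weeks 12 and 16, that is 2 of 4. Safety measures and Safety assessment also speak of following adverse events for up to 16 weeks after the end of intervention. Read literally that is week 8 + 16 = 24, which would make the unrecorded stretch longer still.

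**Step 2. Do other provisions close the gap?**

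- Withdrawal: the SSRI provision covers participants whose symptoms worsen and who leave the study. It does not cover someone who is unimproved but no worse at week 8, starts a drug and keeps attending.
- Herbal restriction: it applies during the study, so it covers follow-up, but it names Chinese herbal treatment only. After week 8 no planned record would show whether it was kept.
- Invalid-data rule: it carries no time limit. If it applies after week 8, the planned records cannot support it.

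**Step 3. Possible size, on assumed figures only.** None of these rates is in the document. Take a generic binary outcome at week 16 with rates pT and pC in the absence of co-treatment. Let a share r of non-responders in each arm start a new treatment and a share s of those then respond. Each rate becomes p' = p + (1 − p)·r·s, so the difference becomes (pT − pC)(1 − r·s). With r from 10% to 40% and s from 30% to 50%, r·s runs from 0.1 × 0.3 = 0.03 to 0.4 × 0.5 = 0.20. Power is for 40 per arm, two-sided alpha 0.05.

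| Assumed rates | Difference without starts | Difference with starts | Power without | Power with |
|---|---|---|---|---|
| 50% vs 30% | 20 points | 19.4 to 16.0 | 45% | 42% to 30% |
| 60% vs 30% | 30 points | 29.1 to 24.0 | 78% | 75% to 58% |

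Under equal start rates among non-responders, the loss is 0.6 to 6.0 points, always towards no difference. Unequal start rates could enlarge the loss or reverse its direction. The model fits a depression-type response most naturally, and no such comparison is specified at week 12 or 16. It shows the mechanism and is not an estimate for NIHSS, mRS or the Barthel Index.

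**The case against.** The strongest reply is that little of importance rests on the follow-up data. The only depression comparison specified is at week 8, wholly inside the recording window. A reader who sees HAMD-17 collected to week 16 might infer that depression is also compared between arms at weeks 12 and 16; the text specifies no such comparison. This part of the reply stands, and the primary result is untouched.

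A reader might also infer that antidepressant use will distort the follow-up results unseen. The document does not support that either. SSRI use for worsening symptoms is tied to withdrawal, and withdrawals are counted as dropouts, so part of it would be visible. Other Chinese herbal treatment is already restricted during the study. What remains is the participant who starts something after week 8 and stays in follow-up, and nothing says how common that will be.

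Nor does the document support a fixed loss. One could assume, say, that 40% of placebo and 20% of JDTLG participants start an antidepressant and half of them respond, giving (0.40 − 0.20) × 0.5 = 10 points. Those rates are invented, and the endpoint they describe is not planned after week 8. TCM syndrome, whose diagnostic signs include low mood or anxiety, is the planned outcome closest to such an effect.

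The invalid-data rule concerns interference with JDTLG, which is no longer given after week 8, so it can fairly be read as confined to the treatment period. The case therefore does not depend on it. The stated aim also does not mention a lasting effect after stopping, and adverse event details are entered on the CRF, which gives some help with attribution.

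None of this answers the central point. Secondary outcomes are assessed at every appointment, two of those appointments have no medication record, and the window is stated explicitly rather than left open. The visit table is not shown; if it lists later recording, it contradicts the text and the two need reconciling.

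**Conclusion.** The point holds as a limited, cheaply corrected weakness. As written, the protocol collects secondary outcomes and safety data at weeks 12 and 16 with no record of treatments started after week 8. Such starts could bias the secondary comparisons at those visits and blur the attribution of follow-up adverse events.

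The size cannot be stated, because the document gives no start rates. The illustrative 0.6 to 6.0 points rests on assumed response rates, equal start rates among non-responders in both arms, and a depression-type endpoint. The direction is towards dilution under those assumptions but is not guaranteed. The conclusion takes the text's stated window at face value. In a single-centre pilot of 80 participants described as not fully powered, this is a modest matter. It still deserves correction, since the results are meant to inform a larger trial and the information is hard to recover afterwards.

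**What to change.** Extend the existing record of medication name, dosage and course, adding start and stop dates, to every visit through the last follow-up visit. If adverse events are indeed followed beyond week 16, the record should run as long.

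Report antidepressant and other relevant co-treatment use by arm beside the week 12 and 16 results. Add a sensitivity analysis of the secondary outcomes at those visits that takes starts after week 8 into account. Its exact form can be left to the analysis plan. Counting starters as failures would not suit NIHSS, mRS or the Barthel Index, since taking an antidepressant is not a neurological or functional failure.

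Recruitment began in April 2017, so some participants may already be past week 8. For them, ask at the next contact and mark the entries as retrospective.

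The cost is a minor protocol and CRF amendment: one more CRF page at two visits that already take place.

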**Table 1 Tab1:**
[figure not shown]
Measurement items and points of data capture

Abbreviations: CT Computed Tomography, MRI Magnetic Resonance Imaging, ECG electrocardiogram, IL interleukin, TC total cholesterol, TG triglycerides, LDL low density lipoprotein, HDL high density lipoprotein, HAMD-17 17-item Hamilton Depression Scale, BI Barthel Index, NIHSS National Institute of Health stroke scale, TCM traditional Chinese medicine.

### Randomization and blinding

A statistician from Xiyuan Hospital GCP Center will generate the randomization code. Eighty participants will be assigned to one of two groups at the ratio of 1:1, whereby the treatment and placebo groups will be coded A and B, respectively. The code will be placed in an envelope and subsequently sealed. The statistician will send the envelope directly to the product manufacturer for labeling of the active and placebo product according to the randomization code. All participants and attending physicians will be blinded to treatment assignment until study completion. Duplicated blinding codes will be given to the research institution and the manufacturer and will not be broken during the trial unless required to do so.

### Data management and quality control

The trial will be conducted according to the ICH Guidelines for Good Clinical Practice in effort to guarantee the rigor of the study. Data will be imported in the clinical data management system (CDMS) available at http://www.xyedc.com, and an independent organization will be responsible for the data management. The investigators are required to attend a series of training sessions which will cover correct administration of the assessments, participant instruction procedures regarding the use of study granules, collection of study variables, CRF completion, and use of the CDMS. Data is to be imported into the CDMS by two independent researchers within 1 week of collection. All discrepant entries will be marked and recorded for resolution at the clinical data system. After the first participant has completed, regular visits will be performed by an independent trial monitor who has been appointed by the trial sponsor. The monitor will review the two entries, resolve discrepancies, and recheck the CRFs and investigators’ source data if necessary.

### Compliance and retention

In order to maximize compliance and retention throughout the study, we will ensure the study schedule and requirements of participation are fully explained prior to obtaining consent, and that participants are aware of the potential risks and benefits of treatment. A copy of the signed informed consent form, containing the contact details of investigators, will be given to each participant so that they are able to contact the principal investigator if required. What is more, all participants will receive a telephone call before each follow-up appointment to remind them of the treatment time and location. Additionally, 8 weeks of medication will be given to participants in two separate sessions to avoid it being misplaced; i.e., at baseline and at week 4. We will try to prevent dropouts by providing ongoing support to participants. Transport allowance, free medical and relative examination will be provided for the participants.

### Sample size calculation

This is an exploratory clinical trial designed to provide scientific rationale and feasibility for clinical phase II pilot study and, therefore, is not fully powered. A sample size of 80 participants will be recruited, with 40 participants in each treatment group. Results from this study will be used to for sample size calculations in future studies.

### Statistical analysis

All of the data from this study will be analyzed by biostatisticians using SPSS 20.0 (IBM Corp., Armonk, NY, USA). Outcomes are based on the intention-to-treat analysis.

Baseline characteristics will be summarized by means of simple descriptive statistics and be compared between two study groups to assess covariate balance. The two-sample Student’s *t* test will be used for continuous variables and the chi-square test or Wilcoxon test will be used for categorical variables.

The primary analysis will be a comparison of the efficacy on depression between the two groups after 8 weeks of treatment. Pearson’s chi-squared test will be used to analyze the effective cases and logistic regression will be used to adjust for chance imbalances in the main prognostic variables between groups, such as age and gender.

Secondary analyses will include the improved cases in neurological function (NIHSS score reduction of ≥ 50% or the total score of 0–1), independence (mRS 0, 1, and 2), daily living (BI scores ≥ 90), and TCM syndrome. Secondary outcome analyses will be carried out according to standard statistical principles for comparison of parametric or non-parametric distributions as appropriate. Logistical regression analysis will be used to adjust for chance imbalances in the main prognostic variables between groups, such as age, NIHSS scores, BI scores, and TCM syndrome scores.

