#### Inclusion criteria

Clinical diagnosis of stroke, showing symptoms of neurological deficitClinical diagnosis of depression according to the DSM-IV or CCMD-3A score of 7–24 on the 17-item Hamilton Depression rating scaleAbsence of psychiatric disease history or family history of psychosis before strokeConscious and cooperative, without aphasia or severe cognitive impairment 2 weeks after strokeHormones or psychotropic drugs not used within 1 month prior to enrollmentNormal liver and renal function testsAged 45–80 years oldDiagnosis of qi deficiency and blood stasis syndrome according to TCM pattern diagnosisAble to provide voluntary signed informed consent

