### Outcomes and measures

#### Primary outcome

The primary outcome is the effectiveness of JDTLG on reducing depression after 8 weeks of treatment. Efficacy defined as a decrease of 50% or more in the 17-item Hamilton Depression Scale (HAMD-17) score or clinical recovery (score < 7) [26].

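### The primary responder comparison has two analyses with no stated order, covariates worded around chance imbalance rather than fixed in advance, and no mention of baseline HAMD-17, to which the endpoint is tied by definition.

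*Protocol article*

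**What the plan says.** All of the analysis text is in the Statistical analysis section of the protocol article.

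- **Baseline.** Characteristics will be summarised and will also "be compared between two study groups to assess covariate balance", using t, chi-square or Wilcoxon tests.
- **Primary comparison at week 8.** "Pearson’s chi-squared test will be used to analyze the effective cases", and in the same sentence "logistic regression will be used to adjust for chance imbalances in the main prognostic variables between groups, such as age and gender".
- **Secondary outcomes.** Logistic regression is again meant to deal with chance imbalances, here in variables "such as age, NIHSS scores, BI scores, and TCM syndrome scores".

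Two other sections matter. Under Primary outcome, response is "a decrease of 50% or more in the 17-item Hamilton Depression Scale (HAMD-17) score or clinical recovery (score < 7"). Under Inclusion criteria, participants enter with a "score of 7–24 on the 17-item Hamilton Depression rating" scale. The Randomization and blinding section gives a 1:1 ratio and describes no stratification by severity.

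**The concern.** Three features of the text combine.

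1. Two analyses are given for one primary comparison, and neither is said to be decisive.
2. The purpose given for adjustment is chance imbalance and the list is open, so the covariate set can be settled after the arms have been compared.
3. The covariate that enters the calculation of the endpoint is not among those named. Age and gender have no such link to response. The secondary list does name the scores of three of its own four outcome scales (NIHSS, BI and TCM, but not mRS), so the principle is applied there and not to the primary scale.

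With 40 per arm, a modest difference in entry severity can pass straight into the response rates. The Sample size calculation section says the results will feed later sample size calculations, so a shifted or selectively chosen estimate would be carried into the next trial.

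**Working it through.** The documents give no response rates, SDs, alpha or power, so there is no stated figure to reproduce. Inputs from the documents are 40 per arm, entry scores 7–24 and the responder rule. Everything marked as assumed is illustrative.

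**Step 1: link between entry score and response.** The highest final score that still counts as a response is max(6, floor(entry/2)). The fall needed is the entry score minus that value.

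| Entry score | Highest final score | Fall needed | % of entry |
|---|---|---|---|
| 7 | 6 | 1 | 14 |
| 8 | 6 | 2 | 25 |
| 10 | 6 | 4 | 40 |
| 12 | 6 | 6 | 50 |
| 18 | 9 | 9 | 50 |
| 24 | 12 | 12 | 50 |

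In points, the hurdle rises across the whole range. In percentages, it is below 50% only for entry scores under 12. This is why the results below depend on whether scores fall by a fixed number of points (additive) or by a fixed fraction (proportional).

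**Step 2: how often severity differs by chance.** Assume a baseline SD of 4.5. The SE of the difference is 4.5 × √(2/40) = 1.01 points. A difference of at least 1 point then occurs in about a third of trials, and of at least 2 points in about 5%.

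**Step 3: what a 2-point difference does when there is no treatment effect.** Simulation with 40 per arm and entry scores normal(14, 4.5), rounded and clipped to 7–24.

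- Additive (mean fall 4, SD 4): two separate sets of runs gave chi-squared rejection of 3.8% and 4.8% with no difference in entry scores, 7.6% and 7.1% at 1 point, 10.4% and 9.5% at 1.5 points, and 14.2% and 13.6% at 2 points. The spurious response difference at 2 points is about 9 percentage points.
- Proportional (mean fall 30%, SD 4): rejection at 2 points is about 8–8.5%, with a spurious difference of about 6 percentage points.
- Logistic model with baseline HAMD-17: rejection at 2 points stays near 5%.

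The figures vary a little with the set-up. One check that held the observed difference at exactly 2 points gave about 11% (additive) and 6.6% (proportional). A repeat for this write-up, holding it within 0.1 of 2 points, gave 13.7% and 8.4%, with spurious differences of 10.5 and 6.8 percentage points.

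**Step 4: overall error rate.** With the imbalance left to randomisation (baseline mean 15.5 with SD 4.5, or mean 18 with SD 3; proportional fall 30%; residual SD 3 or 4), each single method rejected in 1.8–5.3% of null trials. Reporting the better of the chi-squared and baseline-adjusted results gave 4.2–6.1%.

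**Step 5: power.**

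- Additive 3-point effect, uniform entry scores: power rises from 44% to 61% (change SD 4) or from 35% to 43% (SD 5) when baseline HAMD-17 is added. Other runs of additive effects put the gain as low as 6 points.
- Proportional effect (an extra 15 percentage points of fall): 69.4% to 71.8%, 47.4% to 49.5%, 82.0% to 81.2% and 59.0% to 57.8%, a change of about −1 to +2.5 points. One other set of proportional runs showed 3–5 points.

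**Step 6: instability of an imbalance-led covariate set.** If baseline tests did guide the choice, the chance of at least one p < 0.05 among k independent covariates is 1 − 0.95^k: 9.8% for k = 2, 22.6% for k = 5 and 33.7% for k = 8.

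**The case against.** The best defence is that this is a condensed article. Its list is illustrative, and a fuller analysis plan may fix the covariates. An unadjusted test followed by an adjusted analysis is also a common and readable layout. The trial is declared exploratory and "is not fully powered", so lost power matters less and no confirmatory claim rests on the p-value.

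Much of this stands, and it rules out four stronger readings that a reader might infer:

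- **That baseline HAMD-17 is excluded.** The words *such as* exclude nothing. It is not named and not fixed, which is as far as the text goes.
- **That it is the strongest predictor of response.** The document ranks no predictors. Only the structural link in Step 1 follows from it.
- **That baseline p-values choose the covariates.** The balance tests and the adjustment stand in separate paragraphs, and no sentence makes a p-value the rule. Choice after seeing the data is a fair reading of the imbalance wording, but not a stated procedure.
- **That the trial runs a 14% false-positive risk.** That figure needs additive change and a roughly 1-in-20 imbalance, and it applies only to the unadjusted test. Averaged over randomisation, the rate is about 5%.

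The defence does not dispose of the point itself. The complaint is about a rule the article states, not a detail it omits: a plan that follows this wording would tie adjustment to imbalance and leave two candidate primary results. Nor does pilot status help, because a later sample size depends on the estimate, which is what shifts.

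**Conclusion.** The point holds in a moderate form. The primary analysis is not pinned to one method or one covariate set, and the covariate built into the endpoint is not named. The cost is discretion over which result to report, and an estimate that moves with chance differences in entry severity; overall error control is not lost.

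Under an assumed baseline SD of 4.5, a 2-point difference gives the chi-squared test roughly 8–14% false positives and a spurious 6–10 point response difference, against about 5% for the model with baseline HAMD-17. The lower end belongs to proportional change and is soft, since one run gave 6.6%. The power gain is about none under proportional effects and about 6–17 points under additive ones. Because the endpoint is itself mostly a percentage reduction, the proportional case deserves at least equal weight, and power should not be the main argument. All means, SDs and effects are assumptions; only the entry range, the responder rule and 40 per arm come from the protocol. This should be changed, but it does not threaten the trial's validity.

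**What to change.** Name one primary analysis: logistic regression of week-8 response on treatment, baseline HAMD-17 (continuous), age and gender, fixed in advance and used whatever balance is observed. Report the standardised risk difference and the odds ratio, each with a 95% CI. Keep the Pearson chi-squared test as a supportive analysis. Keep the baseline table descriptive, and state that baseline comparisons will not determine which covariates enter any model. Remove the chance-imbalance wording from both the primary and the secondary paragraphs.

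The cost is a few sentences in the protocol or the analysis plan, settled before unblinding. Baseline HAMD-17 is already measured for eligibility, so there is no extra data collection and no change to sample size.

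### The TCM syndrome outcome is graded in four ordered classes but analysed as a yes/no improved case with no cut; an ordinal analysis of the grades would keep the 5% error rate and gain power

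*Protocol article*

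**What the plan says.** Under Secondary outcomes, the protocol article defines the TCM outcome through the relative fall in score from baseline: "The improvement of TCM syndrome at each appointment as measured by the reduction". It sorts that fall into four ordered grades: "clinical cure: reduction > 75%, markedly effective: reduction 51–75%, effective: reduction 25– 50%, invalid: reduction < 25" (per cent). It does not say which grades make a participant improved.

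Under Statistical analysis, the secondary outcomes become counts of improvers. The list opens "Secondary analyses will include the improved cases in neurological function (NIHSS score reduction of ≥ 50% or the total score of 0–1), independence" and closes "daily living (BI scores ≥ 90), and TCM syndrome". NIHSS, mRS and Barthel Index each carry a cut in brackets, and TCM syndrome carries none. A general sentence follows that lets the choice of a parametric or non-parametric comparison depend on the distribution. Logistic regression is then named for adjustment, with the TCM syndrome score among the example covariates.

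On size, the Sample size calculation section says "A sample size of 80 participants will be recruited, with 40 participants in each treatment group" and that the trial "is not fully powered".

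**The concern.** The two sections describe different kinds of outcome. One sets up an ordered scale that separates a participant just past 25% from one past 75%. The other reduces it to yes or no, which treats those two participants alike if the cut is 25%. Nothing in the article explains why the grading is set up and then not used.

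Two things are at stake. With 40 per arm there is little information to spare, and dichotomising a graded scale throws some of it away. Also, the results are meant to feed sample size calculations for later studies, and an improved rate is a poor planning figure if the reader cannot tell which grades it counts.

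**Working it through.** **Nothing to reproduce.** The total of 80 is given without a significance level, power, effect size or rates, and no figure is given for the TCM outcome. The check therefore compares ways of analysing the same four grades.

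**Inputs from the protocol article**
- 40 per arm (Sample size calculation), allocated 1:1 (Randomization and blinding).
- Grade boundaries at 25, 50 and 75% (Secondary outcomes), so three possible cuts: at least 25%, above 50%, above 75%.

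**Assumptions, not in the article**
- Two-sided 5% level, one visit.
- Model A: percentage reduction normal, placebo mean 30, 40 or 50, SD 25 or 30, treatment mean 15 points higher.
- Model B: four control-arm profiles across the grades (invalid / effective / markedly effective / cure), with a common odds ratio of 2 or 3.

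**Tests**
- Single cut (Pearson chi-squared): z = (p_T − p_C) / √[2·p̄(1 − p̄)/40], with p̄ the pooled proportion.
- Four grades: Wilcoxon rank-sum test with mid-ranks and tie correction.
- Under Model B, a control rate c above a cut becomes OR·c / (1 − c + OR·c) on treatment.

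**Model B, one case by hand.** Control profile 25/25/25/25, odds ratio 3, cut at 25%: c = 0.75, and the treatment rate is 3 × 0.75 / (0.25 + 2.25) = 0.90. The two-proportion formula gives 42.1% power and simulation gives 43.6%. The rank test on the four grades has 76.2%.

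**Model B, all cases** (200,000 simulated trials each; power in %; gains in points, taken before rounding)

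| Control profile | OR | ≥25% | >50% | >75% | Rank test | Gain over ≥25% | Gain over best cut |
|---|---|---|---|---|---|---|---|
| 25/25/25/25 | 2 | 22.6 | 33.8 | 29.5 | 39.8 | 17.2 | 6.0 |
| 25/25/25/25 | 3 | 43.6 | 64.9 | 64.8 | 76.2 | 32.6 | 11.4 |
| 40/30/20/10 | 2 | 29.4 | 32.3 | 18.9 | 39.7 | 10.4 | 7.5 |
| 40/30/20/10 | 3 | 57.8 | 68.2 | 43.8 | 76.5 | 18.7 | 8.3 |
| 50/30/15/5 | 2 | 34.0 | 27.0 | 13.1 | 38.4 | 4.4 | 4.4 |
| 50/30/15/5 | 3 | 64.7 | 60.0 | 28.8 | 75.5 | 10.8 | 10.8 |
| 30/35/25/10 | 2 | 25.1 | 34.6 | 18.9 | 39.3 | 14.2 | 4.7 |
| 30/35/25/10 | 3 | 49.2 | 69.7 | 43.6 | 76.2 | 27.0 | 6.5 |

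**Model A.** Across the six combinations of mean and SD, the 25% cut has 30–52% power and the rank test about 53–70%. The gain is about 13–34 points. It is largest when many placebo participants already pass 25%. With placebo mean 50 and SD 25 the rates are Φ((50 − 25)/25) = Φ(1.0) = 84% and, on treatment, Φ((65 − 25)/25) = Φ(1.6) = 95%, which leaves the cut little room to show a difference. At a placebo mean of 50 the 25% cut has 30–35% power and the rank test 54–69%.

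**Error rate with no true effect.** Under Model B, a 25% cut fixed in advance gives 4.9–5.7% and the rank test 4.9–5.0%. The extra power is not bought with a looser test.

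**The case against.** The strongest reply is that the missing cut is only missing detail. The grade below 25% is labelled invalid, so an improved case is naturally any of the other three grades. A full protocol or statistical analysis plan, neither shown here, may say so. An ordered scale reported with an effective rate is also not a contradiction, and the clause on non-parametric comparison leaves room for a rank test. All of this stands, so the point does not rest on the absent cut. That clause permits an ordinal test but does not choose one, and the list and the logistic regression both point to a yes/no analysis.

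A reader might go further and infer that the cut could be picked after the data are seen. Taking whichever of the three cuts is significant would give about 12–14% false positives at one visit instead of 5%. The arithmetic is right, but the article does not show that such a choice is open or intended, and under the natural 25% reading the inflation does not arise.

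Two smaller inferences also fail. The apparent gap between 50% and 51% in the grades is whole-percent notation. Nor is TCM syndrome the target of the trial: the stated aim at the end of the Background is depression and daily living, and the syndrome defines who is enrolled.

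Finally, the trial calls itself exploratory and not fully powered, so low power on a secondary outcome contradicts nothing. That limits the weight of the point. It is no reason to prefer the less efficient analysis when the better one uses the same data.

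**Conclusion.** The point holds as an avoidable loss of information. It is not a demonstrated error-rate problem. Read in the natural way, the planned yes/no analysis of TCM syndrome gives up about 13–34 points of power under a 15-point normal shift, and about 4–33 points under a common odds ratio of 2 or 3, compared with a rank test on the grades that the article itself defines. Against the best of the three cuts under proportional odds the loss is about 4–11 points, but which cut is best depends on grade proportions that are not known in advance.

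The figures rest on an assumed two-sided 5% level, assumed grade distributions and assumed effects; the article gives none of these. The ordinal test was ahead in every scenario examined, and the size of its lead varies widely. The point reaches one secondary outcome only. The HAMD-17 primary analysis and the sample size of 80 are unaffected.

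**What to change.** In the Statistical analysis section, take TCM syndrome out of the list of improved cases and state its main analysis separately: a Wilcoxon rank-sum comparison of the four grades, with a proportional-odds logistic model adjusted for baseline TCM syndrome score. Report the proportion graded effective or better (reduction of at least 25%) as a supportive figure, with that cut written beside it as for the other three outcomes.

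The cost is a few sentences. No new data or visits are needed, the Wilcoxon test is already named in that section for baseline comparisons, and the TCM syndrome score is already among its adjustment variables. The small downside is that an odds ratio across grades is harder to explain than a single rate, and the supportive rate meets that need. The article describes the trial as still recruiting, so on its own account the change could be made before unblinding.
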